## Aims and objectives

The aims of this study are (1) to measure the association between anticoagulation treatments for stroke prevention in AF and time to stroke, systemic embolism (SE), myocardial infarction (MI), major bleeding and mortality among an ARISTOTLE-analogous cohort of patients from UK EHRs, and (2) to develop a methodological framework with in-built validation for using observational EHRs to answer questions about DOAC risks and benefits in patients not included or under-represented in the RCTs.

The specific objectives are to:

Objective 1. Check comparability of EHR data and robustness of methods for measuring stroke prevention medication effectiveness in an ARISTOTLE-analogous cohort using data from EHR data and by comparing with ARISTOTLE results.

Objective 2. Extension of trial findings: measure treatment effects of apixaban in patient groups excluded from ARISTOTLE.

Objective 3. Comparative effectiveness: compare treatment effectiveness between multiple individual anticoagulants (warfarin, apixaban, rivaroxaban, dabigatran) in ARISTOTLE-eligible cohorts and in patient groups excluded from ARISTOTLE.

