## Methods and analysis

Figure 1 (figure adapted from a study in real-world effects of medications for chronic obstructive pulmonary disease^10^) provides an overview of the study, covering the objectives and data sources used, and how RCT data will be used in Objective 1 to validate methods for analysing effectiveness of treatments for stroke prevention in AF in non-interventional data. Should Objective 1 prove successful the validated methods will be applied to unanswered questions in Objectives 2 and 3.

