#### ARISTOTLE

ARISTOTLE was a randomised, double-blind trial completed in 2011, comparing apixaban with warfarin in the prevention of stroke and SE. The trial included 18 201 patients with AF and at least one additional risk factor for stroke. The trial was designed to test for non-inferiority of apixaban compared with warfarin, and showed apixaban superiority for (1) the primary outcome of stroke or SE (HR 0.79, 95% CI 0.66 to 0.95),^7^ (2) the safety endpoint of major bleeding (HR 0.69, 95% CI 0.60 to 0.80), and (3) death from any cause (HR 0.89, 95% CI 0.80 to 0.99). The ARISTOTLE findings led to the National Institute for Health and Care Excellence (NICE) guidelines on stroke prophylaxis in patients with AF recommending apixaban as a treatment. Baseline patient characteristics from ARISTOTLE will be used in selection of participants in Objective 1.

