The absolute rates and HR for the outcomes of interest (time to: stroke/SE, MI, major bleeding and mortality) will then be calculated. For the primary outcome (time to stroke/SE) the EHR results will be validated against the ARISTOTLE trial results using the criteria detailed in the Statistical Analysis section (Validation of observational results against ARISTOTLE data).

#### Objective 2

We will select patient groups who would not have been included in ARISTOTLE (and therefore would not have been included in the Objective 1 cohort) or who are under-represented in ARISTOTLE. Specifically, this will include patient groups such as patients with an AF diagnosis in the EHR cohort meeting these additional criteria:

Severe comorbid condition: disease with a likelihood of causing death within 1 year or reasons making participation unpractical (such as dementia).

When matching the apixaban and warfarin patients within the patient groups for this objective, additional baseline variables will be considered compared with the list specified for Objective 1, Step 2; namely the H, A, and B components of the HAS-BLED score (Hypertension, Abnormal renal/liver function, Stroke, Bleeding history or predisposition, Labile INR, Elderly (>65 years), Drugs/alcohol concomitantly) not included for Objective 1 matching due to being ARISTOTLE exclusion criteria. In these special patient populations the same outcomes as Objective 1 will be assessed, with absolute and relative rates calculated separately in each special patient group.

#### Objective 3

We will select all patients with AF who have a prescription for apixaban, warfarin, rivaroxaban or dabigatran in the treatment period (between 1 January 2013 and 31 July 2019). The ARISTOTLE trial criteria will be applied, followed by matching the warfarin, rivaroxaban and dabigatran ARISTOTLE-eligible EHR patients in turn to the trial-eligible EHR apixaban patients following the methodology outlined in Objective 1, Step 3. This process will result in the creation of three trial-eligible EHR cohorts: warfarin users matched to apixaban users, rivaroxaban users matched to apixaban users and dabigatran users matched to apixaban users. Matched cohorts of excluded patient groups will also be constructed to enable pairwise comparisons of treatment effects in these groups using the method outlined in Objective 2. In all cohorts, the same outcomes as Objective 1 will be assessed with both absolute and relative treatment effects compared.

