#### Validation of observational results against ARISTOTLE data

In Objective 1 alone, we will validate the findings from our primary analysis against ARISTOTLE by determining whether results are compatible with the trial results. ARISTOTLE demonstrated superiority of apixaban over warfarin for the primary endpoint (HR 0.79, 95% CI 0.66 to 0.95).^7^ The treatment effect seen with EHR data may be weaker than that seen in ARISTOTLE.

An analysis of EU patients in ARISTOTLE showed a smaller treatment difference for the primary endpoint and death: HR for stroke/SE 0.92 (95% CI 0.56 to 1.52), all-cause death 0.89 (95% CI 0.68 to 1.18). The European Medicines Agency Assessment Report suggested the smaller treatment effect may have been due to superior INR control in the warfarin arm of the EU subgroup (median time in therapeutic range (TTR) 68.93%)^15^; this study could provide additional evidence on this point.

Either a result of superiority or non-inferiority will be considered compatible with ARISTOTLE results. We have set two criteria that must be met to conclude results are consistent with the trial result:

The effect size must be clinically comparable with the ARISTOTLE findings; the HR for time to stroke/SE with the EHR must be between 0.69 and 0.99. This range is not symmetrical around the ARISTOTLE estimate of 0.79 as it is anticipated the treatment effect in routine clinical care may be weaker than that seen in the optimised setting of a clinical trial.The upper limit of the 95% CI for the rate ratio must be less than 1.52 (upper limit in the EU subgroup of ARISTOTLE).

In addition, if the upper limit of the 95% CI is less than 1 then superiority of apixaban versus warfarin will be concluded.

In order to understand the extent to which the EHR population resembles the ARISTOTLE trial population the absolute event rates of the outcomes will be compared.

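### Only stroke/SE has a validation criterion, yet passing it releases methods called validated for major bleeding, MI and mortality in Objectives 2 and 3

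*Protocol article*

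**What the plan says.** Step 4 of Objective 1 calculates absolute rates and HRs for stroke/SE, MI, major bleeding and mortality. It validates only one of them: "For the primary outcome (time to stroke/SE) the EHR results will be validated against the ARISTOTLE trial results".

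The section on validation against ARISTOTLE keeps to that scope: "In Objective 1 alone, we will validate the findings from our primary analysis against ARISTOTLE". Its two criteria are that "the HR for time to stroke/SE with the EHR must be between 0.69 and 0.99" and that "The upper limit of the 95% CI for the rate ratio must be less than 1.52". The second limit is the stroke/SE figure from the EU subgroup.

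The gate is stated at the start of Methods and analysis: "Should Objective 1 prove successful the validated methods will be applied to unanswered questions in Objectives 2 and 3". The Figure 1 legend likewise calls the techniques validated. For Objective 2, "In these special patient populations the same outcomes as Objective 1 will be assessed", and Objective 3 also uses the Objective 1 outcomes.

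The second aim is a framework that carries its own validation. Its stated use is "using observational EHRs to answer questions about DOAC risks and benefits in patients not included or under-represented in the RCTs". The Background expects estimates of both effectiveness and safety to be comparable with the trial.

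The ARISTOTLE section gives two benchmarks that no criterion uses: "the safety endpoint of major bleeding (HR 0.69, 95% CI 0.60 to 0.80"), and all-cause death at HR 0.89 (0.80 to 0.99). It gives no trial HR for MI.

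Under Methods of analysis, major bleeding follows the on-treatment scheme, and the other secondary outcomes follow the ITT-type scheme.

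**The concern.** The gate depends on the stroke/SE estimate alone, so its result cannot respond to bias in any other outcome. A pass on stroke/SE does not transfer automatically, for three reasons found in the protocol itself.

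- **Different analysis.** The validated analysis follows patients regardless of treatment, whereas major bleeding is censored around the last study drug. Sensitivity analyses says that dropping time after discontinuation may pull safety results towards no difference and risks selection through attrition.
- **Different ascertainment.** Missing outcome data says that strokes of unspecified type make the main safety endpoint uncertain.
- **Different confounders.** The Limitations section reassures on recording of the stroke risk factors, but says it is unclear which codes and what time window define increased bleeding risk. That residual confounding can differ by outcome is statistical reasoning; the protocol does not say it.

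At stake is the meaning of the label. Bleeding and death results in patients excluded from the trial could be reported to NICE, and to the MHRA if they bear on risk and benefit, as products of a validated method when only stroke/SE was checked against a stated rule.

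**Working it through.** The protocol gives no operating characteristics for its criteria, so there is no figure to reproduce. The check has two parts.

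**1. Scope, outcome by outcome**

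| Outcome | Trial HR in the protocol | Numeric criterion in Objective 1 | Assessed in Objectives 2 and 3 |
|---|---|---|---|
| Stroke/SE | 0.79 (0.66 to 0.95) | HR 0.69 to 0.99; upper limit <1.52 | yes |
| Major bleeding | 0.69 (0.60 to 0.80) | none | yes |
| All-cause death | 0.89 (0.80 to 0.99) | none | yes |
| MI | not given | none | yes |

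**2. What a criterion for the other outcomes could do**

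*Precision.* SE(log HR) = ln(U/L)/3.92, and implied events at 1:1 allocation = 4/SE².

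- Stroke/SE: ln(0.95/0.66)/3.92 = 0.093, about 463 events.
- Major bleeding: ln(0.80/0.60)/3.92 = 0.073, about 743 events.
- Death: ln(0.99/0.80)/3.92 = 0.054, about 1354 events.

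The two unused benchmarks are the more precise ones. I assume the same SEs for the EHR cohort; the protocol does not give its expected precision.

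*Pass probability.* For a band (a, b) and a method that targets HR θ: Φ[ln(b/θ)/SE] − Φ[ln(a/θ)/SE].

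*Stroke/SE, band 0.69 to 0.99.*

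- θ = 1.00: Φ(−0.11) − Φ(−3.99) = 0.46.
- θ = 0.79: Φ(2.43) − Φ(−1.46) = 0.92.
- The second criterion does not bind at this precision: at an HR of 0.99 the upper limit is 0.99 × exp(1.96 × 0.093) = 1.19, below 1.52.

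*Major bleeding.* The stroke/SE band is the trial HR minus 0.10 and plus 0.20. Applied to 0.69, that gives 0.59 to 0.89. On the log scale it gives 0.69 × 0.69/0.79 = 0.60 to 0.69 × 0.99/0.79 = 0.86. For 0.59 to 0.89:

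- θ = 1.00: Φ(−1.59) − Φ(−7.19) = 0.056.
- θ = 0.69: Φ(3.47) − Φ(−2.13) = 0.98.
- θ = 0.80: Φ(1.45) − Φ(−4.15) = 0.93.
- θ = 0.85: Φ(0.63) − Φ(−4.98) = 0.73.
- If the EHR SE were 1.5 times larger, the null passes with probability 0.14 and θ = 0.69 with 0.91.

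*All-cause death.* The same tolerance gives 0.79 to 1.09, or 0.78 to 1.12 on the log scale. For 0.79 to 1.09:

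- θ = 1.00: Φ(1.59) − Φ(−4.34) = 0.94.
- θ = 1.05: Φ(0.69) − Φ(−5.23) = 0.75.
- θ = 1.34 (0.89 with an assumed bias factor of 1.5): below 0.001.
- If the trial CI of 0.80 to 0.99 served as the band, a null still passes with probability 0.43.

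A mortality band of this width catches a clearly reversed effect and little else.

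**The case against.** A single prespecified gate on the primary endpoint is a deliberate choice, openly stated, and the bleeding and death HRs are produced anyway, so readers can compare them with the trial. That is fair. It does not explain why one label should cover outcomes the gate does not examine.

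The other outcomes are not ignored. The Abstract promises that absolute and relative risks will be compared with ARISTOTLE, and the validation section compares absolute event rates. Both stand, but both are descriptive: neither has a pass rule or a role in the gate.

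A reader might infer that the matching balances stroke predictors only. The text does not support that. Step 2 chooses variables for the outcomes of interest in general, including renal impairment, alcohol, labile INR and concomitant antiplatelet or anti-inflammatory drugs. Step 3 adds comorbidities. The eligibility criteria exclude increased bleeding risk and conditions likely to cause death within a year, and Objective 2 considers further HAS-BLED components. Residual confounding remains possible, as the protocol concedes, but is not shown.

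The on-treatment scheme is also applied to stroke/SE, as a sensitivity analysis, though outside the gate.

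A reader might also infer that a bleeding criterion cuts the false-pass probability from 46% to about 6%. That holds only for a joint gate and a method that is null on both outcomes. A method null for stroke/SE but right for bleeding would pass a joint gate about 0.457 × 0.983 = 45% of the time (independence assumed).

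Finally, the protocol expects attenuation in routine care, so a bleeding band has a cost: at a true HR of 0.85, about 27% of results fall outside 0.59 to 0.89. That is a reason to set the limits with care in advance, not to omit them.

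**Conclusion.** The concern holds as a mismatch between what is tested and what is called validated. The criteria cover one of four clinical outcomes, the label covers all four, and the bleeding analysis uses a censoring scheme that the gate does not exercise. This falls short of the in-built validation for risks and benefits that the second aim promises.

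For major bleeding the plan leaves out an informative test: on its own tolerance, a null result would pass about 6% of the time and a method targeting 0.69 about 98%. For mortality the gain is limited, since a comparable band passes a null about 94% of the time. For MI the document offers no benchmark.

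These probabilities assume normal log HRs and trial-like precision in the EHR cohort. The documents do not show that the bleeding or mortality estimates will be biased, only that the gate could not tell. An outcome-specific gate would not lower the roughly 46% chance that a null method passes on stroke/SE.

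**What to change.** Make the gate outcome-specific in the validation section, before results are seen.

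1. Add a compatibility criterion for on-treatment major bleeding against the trial HR of 0.69, for example 0.59 to 0.89, or 0.60 to 0.86 on the log scale, with the reasoning for any allowance for attenuation.
2. State that the all-cause mortality HR will be compared with 0.89 (0.80 to 0.99), and that a band on the plan's tolerance (about 0.79 to 1.09) can detect a clearly reversed effect but cannot exclude a null.
3. In Objectives 2 and 3, call an outcome validated only if it met its own Objective 1 criterion. Label MI, and any outcome without a criterion, as not benchmarked.

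If no further criteria are wanted, the minimum is to restrict the word validated to stroke/SE.

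The cost is wording: Step 4 already calculates the HRs, and the bleeding and death benchmarks are already in the text. The downside is that some Objective 2 and 3 outcomes may lose the label.

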
### Exposures, outcomes and covariates

#### Exposures

For all objectives, exposures will be determined using CPRD Gold and Aurum prescribing records and code lists for anticoagulant treatments with no restrictions placed on the dose prescribed.

For Objectives 1 and 2, use of apixaban is the primary exposure of interest and will be compared with warfarin.

For Objective 3, other stroke prevention treatments for AF will also be compared, namely dabigatran and rivaroxaban.

#### Outcomes

Outcomes to be measured are as follows:

Stroke (ischaemic or haemorrhagic) or SE.Major bleeding.MI.All-cause mortality.Time to AF treatment change.

Outcomes will be ascertained using a combination of CPRD, HES and ONS data.

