**Figure 2 F2:**
[figure not shown]
Flow chart illustrating the assembly of a matched trial-analogous cohort of EHR patients. AF, atrial fibrillation; CPRD, Clinical Practice Research Datalink; EHR, electronic health record.

##### Step 1

We will select all (HES and ONS linked) patients in the EHR cohort (CPRD Gold and Aurum) who would have met the following *inclusion* criteria for the ARISTOTLE study, at least 6 months after patient registration in the database on or prior to the index date:

Diagnosis of AF.Age 18+ years.One or more stroke risk factors (age 75 years or older; prior stroke, transient ischaemic attack or SE; congestive heart failure; diabetes mellitus; hypertension).

In ARISTOTLE, patients randomised to apixaban were new users of apixaban while both treatment arms were allowed to be previous users of warfarin, with patients stratified by prior warfarin/VKA exposure. To mirror ARISTOTLE, we will assess trial criteria for apixaban patients on the date of their first prescription of apixaban while allowing patients prescribed warfarin to become eligible at any warfarin prescription date during the study period; furthermore, we will match ARISTOTLE in the proportion of new versus prevalent users in both treatment arms. We will then exclude patients who meet any of the following ARISTOTLE study *exclusion* criteria prior to their eligible-for-inclusion date:

AF due to reversible causes.Mitral stenosis.Increased bleeding risk.Conditions other than AF requiring chronic anticoagulation.Persistent, uncontrolled hypertension.Active infective endocarditis.Current treatment with aspirin >165 mg/day.Simultaneous current treatment with both aspirin and a thienopyridine.Conditions likely to interfere with participation in the trial or cause death within 1 year.Recent alcohol or drug abuse, or psychosocial reasons making study participation impractical.Recent ischaemic stroke (within 7 days).Severe renal insufficiency.Alanine aminotransferase or aspartate aminotransferase >2× upper limit of normal (ULN) or total bilirubin ≥1.5× ULN.Platelet count ≤100 x10^9^/LHaemoglobin <90 g/L.Pregnancy or breast feeding.

Feasibility counts in Gold found approximately 60% of patients with AF prescribed apixaban met the ARISTOTLE trial criteria. Details of the algorithms used in applying the trial criteria to the EHR data are given in the online supplemental file.

10.1136/bmjopen-2020-042947.supp1Supplementary data

##### Step 2

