We will select a subset of apixaban patients from our EHR pool to create a cohort that matches the ARISTOTLE apixaban participants on a selection of the following baseline characteristics:

Age.Sex.Body mass index (BMI).Systolic blood pressure (SBP).Congestive heart failure or left ventricular systolic dysfunction.Hypertension requiring treatment.Diabetes mellitus.Prior stroke/thromboembolism.Smoking status.Alcohol consumption.Level of renal impairment.Prior VKA/warfarin exposure.Labile INR in prior users of warfarin.Concomitant use of: aspirin, antiplatelet or non-steroidal anti-inflammatory drug, lipid-lowering drug therapy, or CYP3A4 inhibitor.

This step will generate a group of ARISTOTLE-analogous apixaban patients, with similar baseline characteristics to ARISTOTLE subjects at the point of randomisation (n~9000).

The variables selected are expected to influence the likelihood of the outcomes of interest. Exact selection of matching variables will depend on the quality and completeness of the data available and a balance will be struck between matched sample size and balance. Different methods to facilitate selection of a matched cohort will be explored, such as propensity score matching (PSM) and coarsened exact matching (CEM),^13^ a non-parametric method that may give estimates with lower variance and bias for a given sample size compared than other methods.^14^

##### Step 3

The resulting trial matched sample of EHR apixaban patients will be matched to the warfarin ARISTOTLE-eligible EHR patients (figure 2) using a matching method such as PSM or CEM (final method selected based on giving optimal sample size vs balance). Risk set sampling will be employed in order to ensure similar duration of prior VKA/warfarin exposure for the prevalent users in the apixaban and warfarin EHR cohorts. The covariates for consideration in matching between EHR treatment arms or construction of a propensity score (PS) model will include the variables listed in step 2 along with additional EHR variables such as data source (Gold or Aurum), socioeconomic status and comorbidities. Each apixaban patient from the ARISTOTLE-eligible EHR patients will be matched 1:1 with the warfarin EHR patient with the closest match giving a trial-analogous cohort of ~18 000.

##### Step 4

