### Statistical analysis

#### Methods of analysis

ARISTOTLE used an intent-to-treat (ITT) approach for the primary efficacy analysis and an on-treatment approach for sensitivity analysis and safety outcomes. We will perform equivalent analyses by using two different censoring schemes: a primary censoring scheme censoring 5 years after index date (reflecting the maximum possible follow-up in ARISTOTLE) for the primary effectiveness analyses, and an on-treatment scheme censoring around time of last study drug for the sensitivity analysis and safety outcome. For the on-treatment censoring scheme, date of last exposure will be estimated using patient prescription data—to allow for drug half life, stockpiling of tablets and less than 100% adherence we will add 30 days after the apparent end of treatment.

Demographic and baseline variables will be presented before and after matching steps. As the primary analysis accounts neither for treatment switching nor discontinuation, the proportion of patients discontinuing treatment and time to treatment discontinuation will be tabulated.

The primary effectiveness endpoint is time to first occurrence of confirmed stroke (ischaemic, haemorrhagic or unspecified type) or SE during the study, regardless of whether the subject is receiving treatment at the time (primary censoring scheme). Comparisons will be made according to prescribed treatment (apixaban vs warfarin).

All time to event endpoints will be analysed using a Cox proportional hazards model including treatment group as a covariate and prior warfarin/VKA status (experienced, naïve). Point estimates and two-sided 95% CIs will be constructed for the outcome. Absolute event rates of all outcomes of interest will also be calculated.

Secondary outcomes cover the key safety outcome of major bleeding and the individual outcomes of stroke, SE, MI and mortality. Secondary outcomes other than major bleeding will use the ITT censoring scheme, major bleeding will use the on-treatment censoring scheme.

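### In VKA-experienced pairs, time to AF treatment change starts at drug initiation for apixaban but mid-treatment for warfarin, so the pooled hazard ratio is not a like-for-like persistence comparison

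*Protocol article*

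**What the plan says.** The Outcomes section lists "Time to AF treatment change" without a definition or an analysis of its own. Methods of analysis then states: "All time to event endpoints will be analysed using a Cox proportional hazards model including treatment group as a covariate and prior warfarin/VKA status". The same section says that "the proportion of patients discontinuing treatment and time to treatment discontinuation will be tabulated", because the primary analysis does not account for switching or stopping.

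The start of follow-up is set in Selection of participants, Objective 1, Step 1. For apixaban, "we will assess trial criteria for apixaban patients on the date of their first prescription of apixaban". For warfarin, the plan is "allowing patients prescribed warfarin to become eligible at any warfarin prescription date during the study period". Step 1 also says "we will match ARISTOTLE in the proportion of new versus prevalent users in both treatment arms". Step 3 adds risk set sampling to "ensure similar duration of prior VKA/warfarin exposure for the prevalent users in the apixaban and warfarin EHR cohorts".

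Objectives 2 and 3 carry the Objective 1 outcomes forward, with absolute and relative effects. Treatment change does not appear in the list of outcomes for rates and hazard ratios in Objective 1, Step 4, nor among the secondary outcomes in Methods of analysis.

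**The concern.** For stroke or death, it is reasonable to align prior VKA duration between the arms. For persistence, the clock that matters is time on the drug being stopped. A VKA-experienced apixaban patient has spent none at index. The matched warfarin patient has already stayed on warfarin for some time, and warfarin users who stopped early and did not restart are not available for sampling at a later prescription.

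If stopping is commoner soon after a drug is started, the apixaban side of these pairs carries the early stopping period and the warfarin side has largely passed it. The VKA-status covariate cannot correct this, because the mismatch lies between the arms within one VKA stratum. A single hazard ratio then mixes a fair new-user comparison (VKA-naive pairs) with one that has unequal time origins (experienced pairs). A reader could take the result as a difference in persistence between the drugs.

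**Working it through.** The plan gives no figure for treatment change, so there is none to reproduce. The check has two parts.

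**1. Time on the index drug at index, from the entry rules**

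| Pair type | Apixaban | Warfarin | Aligned? |
|---|---|---|---|
| VKA-naive | 0 | 0 | Yes |
| VKA-experienced | 0 | prior warfarin duration | No |

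Risk set sampling makes prior VKA duration similar in the second row. It leaves time on the index drug at zero in one arm and above zero in the other.

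**2. Size, with identical drugs (true hazard ratio 1)**

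Inputs from the article: 1:1 matching, about 9000 pairs, censoring at 5 years, Cox model with treatment and prior VKA status.

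Assumed, because the article does not give them: a stopping hazard by time since starting the drug of 0.1 (flat), 0.2, 0.4 or 0.6 per year in the first 6 months and 0.1 per year afterwards, the same for both drugs; experienced warfarin patients entering after 0.5 to 5 years on warfarin; and the experienced share of each arm.

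A hand calculation for experienced pairs with an early hazard of 0.4 uses P(stopped by t) = 1 - exp(-cumulative hazard):

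- By 1 year, apixaban: 0.4 x 0.5 + 0.1 x 0.5 = 0.25, giving 1 - exp(-0.25) = 22.1%. Warfarin: 0.1 x 1 = 0.10, giving 1 - exp(-0.10) = 9.5%.
- By 5 years, apixaban: 0.4 x 0.5 + 0.1 x 4.5 = 0.65, giving 47.8%. Warfarin: 0.1 x 5 = 0.50, giving 39.3%.

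The whole gap arises in the first 6 months, so shorter follow-up makes the hazard ratio larger. The simulated Cox hazard ratios (apixaban v warfarin) show this:

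| Early v later hazard | Experienced pairs, all followed 5 years | Experienced pairs, follow-up uniform over 0-5 years | Pooled, 50% experienced, 5 years | Pooled, 40-60% experienced, uniform 0-5 years |
|---|---|---|---|---|
| 2 times | 1.09-1.14 | about 1.2 | 1.04 | 1.06-1.12 |
| 4 times | 1.36-1.40 | 1.6-1.7 | 1.14 | 1.20-1.32 |
| 6 times | 1.66-1.70 | about 2.1 | 1.25 | 1.30-1.50 |

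VKA-naive pairs followed for 5 years gave 0.96-1.05 in every scenario, which is 1.0 within simulation noise. With a flat hazard, all comparisons gave about 1.0.

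The pooled value also depends on the mix. At 4 times, with 5 years of follow-up, it was 0.99, 1.06, 1.14, 1.29 and 1.40 for 0%, 25%, 50%, 75% and 100% experienced.

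Entry runs from January 2013 to July 2019, and the article notes low apixaban use in its first year. Many patients therefore cannot reach 5 years, and the shorter follow-up scheme is at least plausible.

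**The case against.** Several arguments against the point have force.

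- **The design is deliberate.** It mirrors a trial in which both arms could have used warfarin before and apixaban was new to its arm. Among experienced patients, switching to apixaban versus continuing warfarin is a legitimate strategy contrast. This stands, and it is why those pairs should be labelled as such and not discarded. It does not turn the contrast into a comparison of persistence from drug start.
- **A formal hazard ratio is only implied.** Treatment change is missing from the Step 4 list and from the secondary outcomes, and it plays no part in the validation criteria. This lowers the weight of the point. The general sentence on time-to-event endpoints still covers a listed outcome, and Objective 3 compares the same outcomes in relative terms.
- **The plan already examines switching.** The Sensitivity analyses section commits to looking at patients who switch or discontinue. That is aimed at bias in the on-treatment analyses and does not separate the time origins for this outcome.

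A reader might also infer more than the article supports:

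- *The whole cohort compares starters with established users.* It does not: the mix of new and prevalent users is to match the trial in both arms, and VKA-naive pairs start together.
- *Apixaban is bound to look less persistent.* This requires stopping to be commoner early, and no rates are given. If later warfarin stopping were 0.2 per year (for example, through switching to a DOAC) with an early hazard of 0.4 in both arms, the pooled hazard ratio would be 0.65-0.69. That would be a real drug difference, with the distortion still inside it, but it shows that the observed direction is not fixed.
- *Early warfarin stoppers can never enter.* Those who restart can, since any warfarin prescription may qualify.
- *The discontinuation table misstates dilution of the primary analysis.* It does not. The table describes stopping after index in the same patients, from the same index dates, as the primary analysis. If continuing warfarin users stop less, that arm really is less diluted.

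**Conclusion.** The point holds for VKA-experienced pairs and for the pooled hazard ratio that includes them. The mismatch in time origin follows from the entry rules alone. Its effect depends on a stopping hazard that falls after initiation. Under early stopping 2 to 6 times the later rate and 40-60% of each arm experienced (both assumed), the pooled hazard ratio for identical drugs is about 1.05 to 1.5. It is about 1.0 in VKA-naive pairs, and about 1.0 throughout if the hazard is flat.

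The concern is confined to treatment change read as a between-drug persistence comparison. Stroke/SE, bleeding, mortality and the validation against the trial are not shown to be affected. It is a minor-to-moderate point.

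**What to change.** - Report time to AF treatment change by prior VKA status. Make VKA-naive pairs the main apixaban-warfarin persistence comparison.
- Show VKA-experienced pairs separately, labelled as switching to apixaban versus continuing warfarin.
- Apply the same rule in Objective 2 and in the apixaban-warfarin part of Objective 3.
- Keep the full-cohort discontinuation table, which correctly describes the primary-analysis population, and add a split by prior VKA status.

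This needs analysis wording only: no new data and no change to the cohort, the matching or the primary analysis. The cost is a wider confidence interval for the persistence comparison, because it uses only the VKA-naive patients.
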